### Sample size

The sample size calculation is based on the test of the null hypothesis that the rates of adherence to HAART in the two groups (intervention and control) are equal. The primary measure of effect is the rate of adherence to ART treatment as measured by using the VAS over 6 months. The criterion for significance (alpha) has been set at 0.05. The test is 2-tailed, which means that an effect in either direction will be interpreted. The sample size was calculated using the WINPEPI (PEPI- for-windows) version 9.5 software [26]. With the proposed sample size of 82 in each of the two groups (i.e. assuming a 1:1 allocation ratio), the study will have power of 80% to yield a statistically significant result using a chi-squared test (assuming an intention-to-treat principle for the analysis) of the relative risk at alpha = 0.05. This computation assumes an adherence rate of 80% (for the intervention group) versus 60% (for the control group) at 6 months. These estimates are reflective of estimates from similar studies investigating SMS effect on drug adherences [27] and were modified to account for the type of intervention and patients for this study. We adjusted the sample size for a potential attrition rate of 20% (due to drop-outs) based on attrition rates to care in this centre. Therefore, the required sample size is 198 patients (99 per group). At the YCH ATC, on average, there are about 120 patients put on HAART per month. We estimate that about 90% will have mobile phones and would be eligible to participate in the study. Of these, it is expected that approximately 75% would be willing to participate in the study and will provide consent to participate in the trial. The expected period for recruitment will be one month to obtain 198 patients needed for the trial. It is feasible to recruit 198 patients in one month because we will also recruit from the large pool of old patients. Our study is designed to detect a 20% increase in adherence.

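### The 20% attrition allowance appears to multiply 82 by 1.2 instead of dividing by 0.8, so 198 is 8 patients short; the cost is about one point of power

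*Protocol article*

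**What the plan says.** Everything relevant is in one paragraph of the protocol article, under Sample size.

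- Error rate: "The criterion for significance (alpha) has been set at 0.05". On sidedness: "The test is 2-tailed, which means that an effect in either direction will be interpreted".
- Effect: "This computation assumes an adherence rate of 80% (for the intervention group) versus 60% (for the control group) at 6 months".
- Size before attrition: "With the proposed sample size of 82 in each of the two groups (i.e. assuming a 1:1 allocation ratio").
- Power claimed for that size: "the study will have power of 80% to yield a statistically significant result using a chi-squared test".
- Attrition: "We adjusted the sample size for a potential attrition rate of 20% (due to drop-outs) based on attrition rates to care in this centre".
- Result: "Therefore, the required sample size is 198 patients (99 per group").
- Closing summary: "Our study is designed to detect a 20% increase in adherence".

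The paragraph does not say which formula was used for the attrition step. Elsewhere, the primary objective says that refill data and self-report will fill gaps in the visual analogue scale (VAS). The analysis plan section specifies intention-to-treat with multiple imputation.

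**The concern.** Three statements in the paragraph do not fit together: 82 per group are needed, 20% will be lost, and 99 per group are required. If 20% of 99 are lost, fewer than 82 remain. The figure of 198 is presented as the result of the adjustment, not as a pragmatic round number, so a reader will take it that 80% power survives the stated drop-out.

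At stake is the accuracy of the headline sample size and of the power claim attached to it, both of which would normally be carried into the trial report. The closing sentence adds a smaller problem. It calls the target a 20% increase without saying whether this is absolute or relative, although the same section frames the test in terms of a relative risk.

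**Working it through.** **Inputs**, all from the Sample size section: p1 = 0.80, p2 = 0.60, two-sided alpha 0.05 (z = 1.960), power 80% (z = 0.8416), 1:1 allocation, attrition 20%.

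**Step 1: reproduce 82.** Two-proportion formula, pooled variance under the null, no continuity correction:

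n = [1.960 × √(2 × 0.7 × 0.3) + 0.8416 × √(0.8 × 0.2 + 0.6 × 0.4)]² / (0.80 − 0.60)²

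= [1.960 × 0.6481 + 0.8416 × 0.6325]² / 0.04 = (1.2702 + 0.5323)² / 0.04 = 81.2, rounded up to **82 per group**.

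This matches the plan. Other common variants do not: 91 with continuity correction, 79 with unpooled variance, 81 by arcsine, 87 on the log risk ratio.

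**Step 2: reproduce 99.**

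- Multiplying: 82 × (1 + 0.20) = 98.4, rounded up to 99 per group, 198 in total. This is the plan's figure.
- Dividing: 82 / (1 − 0.20) = 102.5, rounded up to 103 per group, **206 in total**. This is not the plan's figure.

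Working on the total of 164 does not change the picture: 164 × 1.2 = 196.8 and 164 / 0.8 = 205.

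The shortfall is 206 − 198 = 8 patients, or 8 / 206 = 3.9%.

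**Step 3: what 198 delivers.** After 20% loss, 99 × 0.8 = 79.2, so about 79 per group remain. By normal approximation at n = 79:

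power = Φ[(0.20 × √79 − 1.2702) / 0.6325] = Φ(0.802) = **78.9%**.

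| Evaluable per group | Normal approximation | Exact enumeration, uncorrected chi-squared |
|---|---|---|
| 79 | 78.9% | 79.5% |
| 80 | 79.4% | 80.1% |
| 82 | 80.4% | 80.7% |
| 99 (no loss) | 87.2% | 87.7% |

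**Step 4: attrition that 198 does cover.** Setting 99 × (1 − d) = 82 gives d = 1 − 82/99 = **17.2%**.

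**Step 5: label of the effect.** 0.80 − 0.60 = 0.20, which is 20 percentage points. 0.80 / 0.60 = 1.33, a 33% relative increase. The 20 in the closing sentence is therefore the absolute difference.

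**The case against.** The strongest reply is that nothing practical turns on this. The loss is about one point of power by normal approximation and half a point by exact enumeration; on the exact calculation, one more evaluable patient per group restores 80%. The assumed rates come from other studies and were modified for this setting, so their uncertainty far exceeds one point. This stands, and it fixes the weight of the point as minor.

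A second reply is that 79 per group is a complete-case floor. The plan will fill missing VAS values from refill data and self-report and will use multiple imputation, so some drop-outs may still contribute. That is fair, but the document gives no figure from which the recovery could be estimated. The sample size section claims no credit for it either: it treats drop-outs as lost and enlarges the sample for them. An allowance made on that basis should be computed correctly on that basis.

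A third reply is that the multiplication is inferred, because the formula is not printed. This also stands, which is why the allowance only appears to have been computed this way. The mismatch between 82, 20% and 99 holds however 99 was reached.

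On the closing sentence, a reader might take the 20% increase as relative, from 60% to 72%, and conclude that the trial claims 80% power for an effect it is much too small to detect. The documents do not support that reading. The same paragraph prints both rates, 80% and 60%, and 72% appears nowhere. The sentence is loose wording and the calculation is unaffected.

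**Conclusion.** The point holds as a minor error in a stated figure. For 20% attrition on 82 per group the required total is 206, not 198. With 198 randomised and 20% lost, power for 60% versus 80% is about 79%; at 80% power, 198 allows for about 17% attrition.

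These figures assume the plan's own adherence rates, an uncorrected two-sided chi-squared test at 0.05, equal loss in both groups, and no information from patients who drop out. Any gain from imputation would narrow the gap, by an amount the document does not allow one to estimate.

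A reader might infer that the trial is materially underpowered. The figures do not support this: a shortfall of 8 patients and about one point of power would not change how the result is interpreted.

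**What to change.** Keep 198 patients and correct the statement attached to them, in one of two equivalent ways:

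- 198 patients give about 79% power for 60% versus 80% after 20% attrition; or
- 198 patients give 80% power for 60% versus 80% with up to about 17% attrition.

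If the sponsor would rather keep both 80% power and 20% attrition as stated, the total becomes 206 (103 per group).

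In the closing sentence, describe the target as an absolute increase of 20 percentage points (60% to 80%, risk ratio 1.33).

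The cost of keeping 198 is two edited sentences and a slightly less favourable power or attrition figure. It needs no added patients and no change to design, test or analysis.

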### Analysis plan

The analysis and reporting of the results with follow the CONSORT guidelines [28]. The statistician/data analyst will be blinded to the study group. The process of patient selection and flow throughout the study will be summarized using a flow-diagram. The analysis results of patient demographics and baseline outcome variables (both primary and secondary) will be summarized using descriptive summary measures: expressed as mean (standard deviation) or median (minimum-maximum) for continuous variables and number (percent) for categorical variables. We will adopt an intention-to-treat principle to analyze all outcomes, meaning that data from participants will be analyzed according to the group to which they were randomized even if they do not receive the allocated intervention. We will also use multiple-imputation [29] to handle missing data. We will use the T-test for comparing groups on continuous outcomes and the chi-squared test for binary outcomes. All statistical tests will be performed using two-sided tests at the 0.05 level of significance. The Bonferroni method will be used to adjust the level of significance for testing for secondary outcomes to keep the overall level at alpha = 0.05. For all group comparisons, the results will be expressed as effect (or risk ratio for binary outcomes), corresponding two-sided 95% confidence intervals and associated p-values. P-values will be reported to three decimal places with values less than 0.001 reported as <0.001. Adjusted analyses using the following baseline covariates (age, gender, education, duration on HAART, HIV staging, nutritional status (BMI) and the presence or not of an opportunistic infection (OI)) will be performed using regression techniques to investigate the residual impact of key baseline characteristics on the outcomes. Goodness-of-fit will be assessed by examining the residuals for model assumptions and chi-squared test of goodness-of-fit. All analyses will be performed using SPSS (Statistical Package for the Social Sciences) version 16.0 for Windows.

Adherence will be measured both as a continuous outcome (change in adherence) and as a binary outcome i.e. adherent (95% of pills taken) or non adherent (< 95% of pills taken). In literature, adherence data can be handled in a number of ways. The measures can be reported as the number of doses respected or can be combined into a composite score [21]. Even though combined measures are more correlated to clinical response, they are not very practical [22]. The data from the various adherence measures will not be merged. We will report the effects of the intervention on all the measures of adherence used, and compare them for discrepancies.

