### Participants: inclusion/exclusion criteria

We will include subjects who are aged above 21 years, own a mobile phone and can read text messages, and who have been on HAART for at least a month. Informed consent is a prerequisite for participating in the study, and will be provided orally and in writing.

We will exclude participants who have been on HAART for less than a month, are aged less than 21 years. Participants who have used HAART for at least one month are chosen so that we can calculate a baseline figure for adherence.

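### Baseline adherence is collected, but neither the primary chi-squared test nor the adjusted analysis of the 6-month binary outcome uses it, which gives up precision at almost no saving

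*Protocol article*

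**What the plan says.** The eligibility section of the protocol article gives the reason for the one-month rule: "Participants who have used HAART for at least one month are chosen so that we can calculate a baseline figure for adherence". The Randomization section has adherence recorded at baseline, 3 months and 6 months. It describes random blocks of 2, 4 and 6 and names no stratification factor.

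Table 1 defines the primary outcome as binary, VAS above 95% at 6 months, compared by a chi-squared test. The Sample size section rests on the same test: "the study will have power of 80% to yield a statistically significant result using a chi-squared test".

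The Analysis plan adds regression analyses with a closed list of seven covariates: "Adjusted analyses using the following baseline covariates (age, gender, education, duration on HAART, HIV staging, nutritional status (BMI"), and lastly the presence of an opportunistic infection. Baseline adherence is not among them.

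Baseline adherence has two other uses. Baseline values of the outcomes are summarised descriptively. Adherence is also analysed as a continuous change, and the Table 1 footnote assigns a t-test to the continuous version of all three measures.

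**The concern.** A baseline measurement of the outcome is usually a natural covariate for the later value. Here an entry criterion exists to make that measurement possible. The two planned analyses of the binary primary outcome both leave it out, and randomisation is not described as stratified on it.

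At stake is precision. If baseline and 6-month adherence are correlated, part of the outcome variation could be removed at no extra data cost. That would give a narrower confidence interval for the risk ratio and more power at the same sample size. A baseline-adjusted analysis of the binary outcome that is added after the data are seen would be post hoc, so it needs to be named beforehand.

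**Working it through.** **Inputs from the Sample size section.** "The criterion for significance (alpha) has been set at 0.05"; "The test is 2-tailed, which means that an effect in either direction will be interpreted"; "This computation assumes an adherence rate of 80% (for the intervention group) versus 60% (for the control group) at 6 months"; "With the proposed sample size of 82 in each of the two groups (i.e. assuming a 1:1 allocation ratio").

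**Inputs assumed.** The document gives neither the correlation r between baseline and 6-month adherence nor the proportion adherent at baseline. I take r as a range and 60% adherent at baseline, equal to the assumed control rate at 6 months.

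**Step 1: reproduce the plan's figure.** With pooled variance under the null and mean rate 0.7:

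n = [1.960·√(2·0.7·0.3) + 0.842·√(0.8·0.2 + 0.6·0.4)]² / 0.2² = (1.270 + 0.532)² / 0.04 ≈ 81.2, rounded up to 82 per group.

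Power at 82 = Φ[(0.2·√82 − 1.270) / 0.632] = Φ(0.855) = 80.4%. The stated 82 and 80% reproduce for the unadjusted test.

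**Step 2: effect of adjusting for baseline.** Adjustment multiplies the residual variance by about 1 − r², so 82 per group act like 82/(1 − r²). At r = 0.3 that is 82/0.91 = 90.1, and power = Φ[(0.2·√90.1 − 1.270)/0.632] = 84.0%.

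**Step 3: check by simulation.** There were 40,000 simulated trials per setting, with 82 per group, 60% adherent at baseline, and 80% versus 60% at 6 months. The comparison is the chi-squared test against a Mantel-Haenszel test stratified by baseline adherent yes/no.

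| r | Power by formula, adjusted | Simulated, unadjusted | Simulated, stratified |
|---|---|---|---|
| 0 | 80.4% | 80.9% | 80.6% |
| 0.2 | 82.0% | 81.0% | 82.4% |
| 0.3 | 84.0% | 80.5% | 84.1% |
| 0.4 | 86.8% | 80.8% | 86.9% |
| 0.5 | 90.3% | 80.9% | 90.5% |

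Type I error of the stratified test was 4.9% to 5.0%.

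**Step 4: how plausible is the top row?** With 60% adherent at baseline and 80% at 6 months, the share of baseline-adherent patients still adherent at 6 months is 0.8 + r·√(0.6·0.4·0.8·0.2)/0.6 = 0.8 + 0.327r. At r = 0.5 this is 96%. It reaches 100% at r = 0.2/0.327 ≈ 0.61, the largest value possible. So 0.5 is an optimistic case.

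**Step 5: does the change score recover the loss?** Relative to the variance of the 6-month value, and with equal variances at the two times, a change score has factor 2(1 − r) and baseline adjustment has 1 − r². At r = 0.3 these are 1.40 and 0.91. At r = 0.5 they are 1.00 and 0.75. Below r = 0.5 the change score is noisier than the 6-month value alone.

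**The case against.** The strongest reply is that nothing is wrong with the primary test. A chi-squared test is valid in a randomised trial, the trial was sized for it, and the sizing reproduces. The adjusted analyses are supportive. All of this stands, and it limits the point to efficiency. It does not remove the point: the article itself fixes both the test and the covariate list, so this is a stated choice and not a detail left to a later plan.

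Four stronger readings are tempting, and the document does not support them.

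- **That baseline adherence is collected for no purpose.** It is summarised descriptively and it enters the change in adherence.
- **That a chance baseline imbalance would make the result untrustworthy.** Chance imbalance is already covered by the 5% error rate and the confidence interval of the unadjusted test. The consequence is a wider interval, not invalid inference.
- **That the omission leaves the trial below 80% power.** At 82 evaluable per group the unadjusted power is 80.4%. Whether 99 randomised per group will leave 82 is a separate question about the attrition allowance.
- **That a gain of several points is assured.** At r = 0 there is none, and at r = 0.2 it is between one and two points.

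A last objection is that replacing the primary test goes further than the gap requires. The minimum repair is indeed to extend the covariate list. Making the adjusted comparison primary is a preference, supported by the near absence of a downside: at r = 0 the simulated loss is 0.3 points.

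**Conclusion.** The omission is plain in the text, and correcting it is a nearly free improvement. The planned primary analysis is unbiased and has its stated power. What is given up is precision. At 82 per group, stratifying on baseline adherence would take simulated power from about 81% to 82%, 84%, 87% or 90% at correlations of 0.2, 0.3, 0.4 or 0.5, with no gain at zero.

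These figures rest on the protocol's 80% versus 60%, on an assumed 60% adherent at baseline, and on a correlation that the document does not supply. The omission is certain; the size of the gain is not. The change score for continuous adherence does not make up the difference, because it is less efficient than baseline adjustment at any correlation below 1 and concerns a different form of the outcome.

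**What to change.** In the Analysis plan:

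1. Add baseline VAS adherence to the covariates for the adjusted analyses.
2. Pre-specify a baseline-adjusted risk ratio for the 6-month binary outcome: either a Mantel-Haenszel risk ratio stratified by baseline adherent yes/no, or a regression-standardised risk ratio with baseline VAS as covariate. Both keep the risk-ratio scale already promised for binary outcomes.
3. Preferably make this the primary comparison and keep the unadjusted chi-squared test as supporting. If the chi-squared test stays primary, name the adjusted risk ratio as the main sensitivity analysis.
4. For continuous adherence, replace the t-test on change with ANCOVA of the 6-month value on group and baseline.

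The cost is analysis wording and about one degree of freedom. No new data are needed. The 82 per group need not be recalculated for this change, since the unadjusted calculation corresponds to the no-correlation case. If the primary test changes, Table 1 and the Sample size section should say so, and the choice should be fixed before outcome data by group are seen.

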### Additional studies

• **Adherence rates: **We will use this opportunity to calculate the rates of adherence to HAART in the YCH ATC. The context of adherence to HAART in Cameroon has changed greatly over time and the rates reported in literature were subject to cost (which has been dropping over time), availability, accessibility, study design, technique used to measure adherence and study setting. These rates vary from 10% to 97% [30-32]. This study will provide a more accurate and current estimate of adherence in Cameroon.

• **Safety: **Data will be collected on issues that may arise from the use of text messages to improve adherence.

• **Health worker experiences: **Self-administered questionnaires will be used to assess health worker perceptions of the intervention in terms of long term use, additional workload and benefits to care. The applicability of such an intervention will depend largely on its acceptability by health workers.

### Ethical Considerations

The trial will be conducted in compliance with the local protocol and applicable regulatory requirements in Cameroon. The study has been approved by Cameroon National Ethics Committee. Any deviations from the protocol will be reported and explained. The study will be conducted in accordance with the Helsinki declaration [33] and other established clinical practice guidelines for research on human subjects. Research personnel will approach all potentially eligible patients who fulfill eligibility criteria for consent. All patients must sign a consent form to participate in the trial.

## Discussion

The potential of mobile phone technology to improve health outcomes is a domain worth exploring, especially in this era of increased uptake and dependence on mobile phones. Studies investigating the use of text messages to improve adherence have yielded varied results [12,16,34].

Improving adherence to HAART can play a key role in reducing morbidity and mortality due to HIV, the occurrence of drug resistant strains and the waste of medication in health systems that are already seriously challenged by the advent of HIV. Findings generated from this trial may be generalized to other chronic illnesses.

A major ethical consideration is the harm that may arise due to accidental disclosure of status. This eventuality will be properly explained to the participant, even though our message will neither disclose status nor medication. In a study evaluating the use of mobile phones to improve attendance to an HIV clinic in Uganda, privacy and confidentiality were not a problem [35]. Loss of privacy was not identified as a deterrent in the HIVIND trial [8,36]. We are aware that most mobile operators in Cameroon deliver mass text messages to their clients for business, advertising, information and sometimes health. Our intervention will be an addition to an already existing system. Another concern is how to manage text messaging on a larger scale, knowing fully well that it cannot be left in the hands of mobile operators, who will then be privy to the phone numbers of potentially identifiable individuals. In this trial, the operators will not be used because a framework for cooperation that will not jeopardize confidentiality and anonymity hasn't been established. A single phone with prepaid airtime will be used to deliver the text messages.

This intervention centers on the Health Belief Model of behavior change [37]. We will collect data on modifying factors (socio-demographic and disease related), perceived barriers to adherence and test the efficacy of the SMS reminder as a cue to action. Putting all these in context will provide a better picture of who doesn't adheres to HAART, why they don't adhere and if text messages can help. Applying the SMS not only as a reminder, but as a cue to action permits it use to resolve intentional and non-intentional non-adherence. In addition, we will open channels for communication between appointments. Galovotti et al succinctly describe the key components of an intervention aimed at bringing about a change in behavior. The use of role models, affective impact, and links to socio-cultural narratives, personalization and knowledge of impediments and facilitators are important features of successful behavioral interventions [38].

Finally, this trial may contribute to the growing body of evidence on the use of mobile phone technology to improve health outcomes in low resource settings.

